**Trial registration number:**

NCT02688751.

Strengths and limitations of this studyFirst comparison of contrast-enhanced ultrasound to a dynamic form of CT imaging, representing a methodological improvement.Both imaging modalities occur on the same day removing changing findings as a confounding factor.Primary outcome set as type I/III endoleak (most clinically significant) rather than all endoleaks.Appropriately powered but small study.Single-centre study.

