Systematic review of the diagnostic accuracy of CEUS (in comparison to CTA) in detection of any endoleak revealed variable sensitivity ranging from 67% to 100% and specificity ranging from 79% to 100%.^17^ The value of this review is compromised by heterogeneity of contrast material used and non-reporting of ultrasound imaging technique used, specifically whether colour duplex combined with contrast or harmonic CEUS imaging was used. There are potentially additional reasons for variability in the reporting such as operator dependence, quality of equipment used as well as body habitus of the patient. The consideration that neither CEUS nor single-phase CTA represent gold standard of endoleak diagnosis led to the metanalysis^14 17^ adopting a bivariate model of analysis. This approach does not compensate for the lack of gold standard comparator as it favours any modality producing false positives. Comparison against the gold standard has never been established for either modality.

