### Outcome measures

The primary outcome is:The predictive values of CEUS in comparison to tCTA (as comparator) to detect stent graft-related endoleaks.

Secondary outcomes are:Any adverse events during CEUS or tCTA.Predictive values of CEUS in comparison to tCTA to detect type II endoleaks.Predictive values of both tCTA and CEUS in predicting final endoleak diagnosis (following any further investigations).Predictive values of both tCTA and CEUS in predicting need for a secondary intervention.Evaluate the association between CEUS temporal delay (difference between contrast in endograft and contrast in endoleak) and evaluate its ability to improve the differentiation of endoleak type.Evaluate the association between ‘CEUS contrast in endoleak’ to ‘tCTA contrast in endoleak’ and assess potential as predictive tool, for optimum timing of CTA phases.

Analysis plan

Associations will be established/refuted with summary statistics and graphical analysis and appropriate further statistical testing within the framework of logistic regression. If association can be established, then predictive modelling will be undertaken. The agreement between CEUS and tCTA will be evaluated with Kappa statistic.^25^ Sensitivity/specificity will be calculated along with binomial exact 95% CIs and leave-one-out cross-validation. We will also report the positive predictive value and negative predictive value.

The power calculation^26^ showed the required sample size to be 74. This was calculated based on a prevalence of stent graft-related endoleaks of 11% as demonstrated on previous tCTA studies of endoleaks. It was powered to detect a predicted sensitivity of 0.95 with a tolerated CI of ±0.15. The study commenced recruitment in February 2016 and is ongoing.

Monitoring and data

All patients referred to the study are recorded in the screening log. The sponsoring trust will provide governance oversight and annual reports to the ethics committee will provide ethical overview. Radiation exposure of participants will be monitored and reported to the sponsors and approving research ethics committee. No interim analysis is planned.

On completion of the study, all identifiable patient demographics will be removed and anonymised data will be stored to allow for future analysis of unforeseen benefits. During the study, data are stored in a secure manner within the host institutions data management processes. Access is restricted to the investigators and for audit by the sponsor.

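### The sample size of 74 assumes sensitivity of 0.95 ± 0.15 by a large-sample formula, but the planned exact intervals are unlikely to be that narrow with about 8 positives

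*Protocol article*

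**What the plan says.** All the inputs are in the Protocol article, under Outcome measures (Analysis plan paragraphs).

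- Sample size: "The power calculation^26^ showed the required sample size to be 74".
- Prevalence: "This was calculated based on a prevalence of stent graft-related endoleaks of 11" per cent, taken from earlier tCTA studies.
- Precision target: "It was powered to detect a predicted sensitivity of 0.95 with a tolerated CI of ±0.15".
- Interval method for the analysis: "Sensitivity/specificity will be calculated along with binomial exact 95% CIs".
- Primary outcome: "The predictive values of CEUS in comparison to tCTA (as comparator) to detect stent graft-related endoleaks".

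The strengths and limitations list, after the trial registration number, describes the trial as "Appropriately powered but small study". The article does not state how many reference-positive patients it expects.

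**The concern.** Sensitivity is estimated only in patients whom tCTA classifies as positive. At 11% prevalence, 74 participants give about 8 of them. A half-width of 0.15 around 0.95 is not credible from 8 binary observations, and the upper end would exceed 1. The planning statement and the planned exact intervals therefore appear to rest on different methods.

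Sensitivity for stent graft-related endoleak is the quantity the study was sized on, and the article treats this endoleak type as the most clinically significant. A reader told that the design delivers 0.95 ± 0.15 could over-read a perfect result. If all 8 expected cases are detected, the planned interval still includes a true sensitivity of 63%.

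**Working it through.** **Inputs.** N = 74, prevalence 0.11, predicted sensitivity 0.95, half-width 0.15, two-sided 95% exact (Clopper-Pearson) interval. All are from the Analysis plan paragraphs.

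**Step 1: reproduce the 74.** Wald precision formula for the positives, divided by prevalence:

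- positives = 1.96² × 0.95 × 0.05 / 0.15² = 8.11
- N = 8.11 / 0.11 = 73.7, rounded up to 74

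The stated figure is reproduced. (Rounding the positives up to 9 first would give 9 / 0.11 = 81.8, so 82; the article did not do this.)

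**Step 2: is the formula usable here?** With 8 positives the Wald half-width is 1.96 × √(0.95 × 0.05 / 8) = 0.151, so the interval is about 0.80 to 1.10. The upper end is not a possible sensitivity. An estimate of 0.95 cannot occur with 8 positives either; the nearest values are 7/8 = 0.875 and 8/8 = 1.00.

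**Step 3: apply the planned exact interval.** Expected positives = 74 × 0.11 = 8.14. When all n are detected, the exact lower limit is 0.025^(1/n).

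| Detected / positives | Exact 95% CI | Width |
|---|---|---|
| 7/8 | 47.3–99.7% | 0.523 |
| 8/8 | 63.1–100% | 0.369 |
| 11/11 | 71.5–100% | 0.285 |
| 14/14 | 76.8–100% | 0.232 |
| 17/17 | 80.5–100% | 0.195 |

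If the true sensitivity is 0.95 and there are 8 positives, 8/8 has probability 0.95⁸ = 0.66 and 7/8 has probability 8 × 0.95⁷ × 0.05 = 0.28. A Wilson interval for 8/8 is 67.6–100%, so the shortfall does not depend on the choice of Clopper-Pearson.

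**Step 4: let the number of positives vary.** Positives follow Binomial(74, prevalence); those detected follow Binomial(positives, 0.95). At 11% the central 95% range is 3 to 14 positives, and the chance of fewer than 8 is 42%. The 20% and 25% rows are assumptions; the article gives no such figures.

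| Prevalence | Expected positives | Mean exact width | P(width ≤ 0.30) | P(lower limit ≥ 0.80) |
|---|---|---|---|---|
| 11% (article) | 8.1 | 0.45 | 10% | 0.1% |
| 20% (assumed) | 14.8 | 0.30 | 54% | 12% |
| 25% (assumed) | 18.5 | 0.26 | 72% | 26% |

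The last two columns are two readings of ±0.15: a total width of 0.30, or a lower limit of 0.80. With no missed cases, the first needs 11 positives and the second 17, since ln 0.025 / ln 0.80 = 16.5.

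**The case against.** Several points on the other side have force.

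- **The arithmetic is right.** The 74 follows from its formula, so this is not a calculation error. That stands. The fault is that the formula does not hold at about 8 positives and does not match the interval planned in the same section.
- **The target is not out of reach.** A reader might infer that 63–100% is a ceiling, or that ±0.15 cannot be met. The numbers do not support that: 11/11 has a width of 0.285, and at 11% prevalence the width is 0.30 or less about 10% of the time. Unlikely is the correct word.
- **A lower limit of 0.80 is only one reading.** The article names no lower limit, so the 0.1% figure should not stand alone. The more lenient width reading still fails about nine times in ten at the planned prevalence.
- **Prevalence may be higher.** Under Participants, those enrolled are typically under suspicion of a graft-related endoleak or aneurysm expansion. At an assumed 20–25% the planned width is met on average. This limits the certainty, but 11% is the figure the article plans on.
- **The 0.95 may look optimistic** beside the Background's "variable sensitivity ranging from 67% to 100% and specificity ranging from 79% to 100" per cent. That range concerns any endoleak compared with CTA, not stent graft-related endoleak compared with tCTA. It is not evidence against 0.95 here, and a larger sample size derived from a lower sensitivity would have no figure in the article behind it.
- **The article admits the study is small, and the exact intervals will show the imprecision.** Both are true, but the same line also asserts adequate power, and that is the part that fails.

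**Conclusion.** The concern holds as a mismatch between planning formula and analysis method. At the article's own 11% prevalence and predicted sensitivity of 0.95, the planned exact interval averages 0.45 wide against the intended 0.30, and has about a 10% chance of being 0.30 or narrower. Its lower limit reaches 0.80 about 0.1% of the time. The claim of appropriate power is therefore not supported.

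This rests on 11% prevalence and on Clopper-Pearson as the exact method. If prevalence were 20–25%, the width target would be met on average, but a lower limit of 0.80 would still be reached only 12–26% of the time. The finding does not show that 74 was miscalculated, that the precision is unattainable, or that 0.95 is the wrong planning value.

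**What to change.** Keep the 74 participants and replace the precision sentence. For example: 74 participants at 11% prevalence are expected to yield about 8 tCTA-positive cases (95% range 3–14); the exact 95% CI for sensitivity would be 63–100% if 8 of 8 are detected and 47–99.7% if 7 of 8 are detected. If a higher-prevalence scenario is added, label it as an assumption.

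Remove the statement that the study is appropriately powered from the strengths and limitations list; the acknowledgement that it is small can stay. As an option, add the precision for specificity, which rests on about 66 negatives (74 − 8) and is better estimated: 66/66 would give 94.6–100%.

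The cost is wording only, with no extra participants and no change to the tests or the analysis. The stated precision becomes less favourable. The article reports recruitment as ongoing, so the change can be made before results are known.
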